**Fig. 1 Fig1:**
[figure not shown]
Flow chart including intervention and assessments of anxiety, pain and physiological parameters during a day, which will be repeated at BL, W1 and W2

**Fig. 2 Fig2:**
[figure not shown]
Flow chart including interventions and assessments related to sensorimotor function and health-related quality of life

A summary of outcome assessments in relation to hypotheses and assessment methods can be found in Table 1.

For describing the study group, disability after stroke will be assessed by the Barthel index [42] and mRS [43]. In addition, age, gender, location of lesion, and acute treatment (thrombolysis/thrombectomy) will be recorded.

In this study we will attempt to assess components of body function such as anxiety, pain, and stress response. To test **hypothesis I** we will assess anxiety (primary endpoint) with the State-Trait Anxiety Inventory (STAI) [39]. Traits (A-Trait) are found to be stable over time and not sensitive to occasional stressors. These will be used at BL, W2, and FU. States (A-State) are found to be sensitive for occasional stressors assessing current emotional state [39] and will be used before and after treatment at BL, at W1 and W2. Pain will be assessed with a Visual Analogue Scale (VAS) [44]. To test **hypothesis II** (stress responses) we will record HRV as a continuous recording of a single-channel electrocardiogram (ECG) during TM at BL, W1 and W2. Salivary cortisol and blood pressure will be assessed in the morning, before and after TM and in the evening at BL, W1 and W2.

Further, we will assess effects on aspects related to activities as classified in ICF. Due to the limited amount of knowledge in this area and the heterogeneous sample, we will include a wide spectrum of assessments evaluating different aspects of activities. **Hypothesis III** (sensorimotor function) will be assessed with the Shape Texture Identification Test (STI) [45] to assess tactile gnosis, at PBL, BL, W2 and FU. STI has been found to have satisfactory validity and reliability [46, 47]. Box and Blocks test [48] will be used to test gross dexterity at PBL, BL, W2 and FU. The reliability and validity have been tested in several studies among different groups and found to be satisfactory [48]. To test fine motor dexterity, the Nine Hole Peg test [49] will be used at WBL, BL, W2 and FU. The Nine Hole Peg test has appropriate psychometric properties used among people following stroke [49]. The Jamar® Hydraulic Hand Dynamometer [50] will be used to assess grip strength, at WBL, BL, W2 and FU. Validity and reliability tests among healthy women have been satisfactory [51]. All sensorimotor tests will be performed based on standardized instructions with two trials for each hand starting with the unaffected hand. A movement laboratory with high-speed cameras will be used to perform advanced movement analysis with respect to quality in motor performance of hand and arm movement. Temporal and spatial kinematic variables will be evaluated. The participants will be evaluated pre- and post-intervention during functional manipulative tasks, such as the NineHole Peg test [49] and the Finger Nose test [52]. To test **hypothesis IV** the Barthel index and mRS will be used to assess ability after stroke at BL, W2 and FU. **Hypothesis V** will be tested in subsample 1 by evaluation of brain activity conducted on a GE 3 T scanner (General Electric, USA) in collaboration with the Umeå Center for Functional Brain Imaging (UFBI, Norrlands University hospital). The participants will perform finger movements with the paretic hand in the MR scanner while simultaneously recording the movements with special high-speed cameras, at BL and W2.

To assess effects on participation we will assess HRQoL with the Nottingham Health Profile (NHP) [53] which is a self-rating scale. NHP has been found to be a valid and sensitive measure of HRQoL [54] and is recommended to be used among people following stroke [55]. NHP will be used at BL, W2 and FU.

The assessments will be recorded on paper forms and the blinded assessor will provide each form with an ID code and store the code list in a locked cabinet. The first author will be responsible for the data entry of the coded paper forms.

### Data analysis

Data will be analyzed with repeated measurement methods to compare the intervention group and the control group. Statistical regression models that adjust for background characteristics and account for correlated measurements for the same individual will also be used (e.g., mixed effects model and generalized estimating equations). Data will be analyzed by inter-group analyses using the Statistical Package for Social Science (SPSS). Effect size will be estimated with Cohen’s d. The analysis will be performed on an intention-to-treat basis.

HRV will be analyzed by automatic detection of heartbeats, then the R-R interval data will be derived and transformed into an evenly sampled heart rate time series. From this time series HRV will be analysed in the frequency domain where the relative influence of different spectral components will be determined. From the signal, the mean heart rate, the total spectral power (PTOT), and the power of the low-frequency (PLF; 0.04-0.15 Hz) and high-frequency (PHF; 0.15-0.40 Hz) will be calculated. The recording and analysis software has been developed at Department of Biomedical Engineering (DBE), Vasterbottens county council (VLL) and will be analysed in collaboration with DBE, VLL.

The fMRI data will be analyzed in collaboration with experts at the UFBI. The effects of TM on sensorimotor functions and brain activity over time will be studied and compared within and between the intervention and control groups. The analysis will be similar to an earlier fMRI study [56].

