Stroke causes neurological deficits and it is therefore important to find interventions during the rehabilitation phase that can regain the patient’s abilities and promote neuronal recovery or compensation. Grefkes & Flink [32] argue that recovery from stroke is driven by neuronal reorganization in the brain. Studies using fMRI show that movements in the paretic limb induce abnormal activity in motor-related areas (both contralesional and ipsilesional hemispheres) compared to more focused activity in motor-related areas (contralateral hemisphere) in healthy controls. Furthermore, longitudinal studies have found that in subjects with good recovery, abnormal activity in motor-related areas is decreased and reaches levels similar to those found in healthy controls [32]. Some studies have evaluated brain activity in relation to motor rehabilitation after stroke [33]. The findings showed that in those who successful recovered following treatment, there was a shift from brain activity mainly in the contralesional motor cortex to activity mainly in the ipsilesional motor cortex when activating the affected limb. Also, stimulation of other senses after stroke, like visual stimulation by mirror therapy, affected the reorganization of brain activity toward the ipsilesional hemisphere [34]. The group participating in mirror therapy also improved according to the Fugl-Meyer motor assessment [34]. Results from the aforementioned studies suggest that successful treatment may normalize brain activity. However, as far as we know, no study has evaluated recovery after somatosensory stimulation by TM with respect to brain activity in stroke patients. It has been found, however, that sensory stimulation in stroke patients increase motor recovery, although the mechanisms are unknown [23].

Despite the often high quality of stroke care, decreased general health and independence are frequent in stroke survivors, and there is a need to further improve treatment and rehabilitation. Based on earlier research there are reasons to believe that TM may decrease anxiety, pain, stress reactions, and effect sensorimotor function after stroke and thus has the potential to improve everyday life after stroke. There is therefore reason to further evaluate the effects of TM after stroke.

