## Participants

### Participants

#### Inclusion criteria

Fifty participants will be recruited from two stroke units in northern Sweden within one week after the onset of stroke. The inclusion criteria will be 1) acute stroke defined according to the WHO-criteria of a neurological deficit of cerebrovascular cause that persists beyond 24 h [36]. The stroke cases are classified according to the TOAST (Trial of Org 10172 in Acute Stroke Treatment) [37] and OCSP (Oxford Community Stroke Project) [38] systems, 2) impaired finger tapping on the affected side of the body, 3) visible volitional flexion of the fingers on affected side of the body.

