### Assessments

Some of the effects are expected to occur immediately after a TM session and will be assessed before, during, and after the intervention session by the massage therapist (Fig. 1) on three occasions: baseline (BL), after one week (W1), and after two weeks (W2). Other effects are expected to occur over time and will be assessed on four occasions by a blinded assessor without knowledge of group affiliation. One occasion is a pre-baseline assessment in order to exclude the possibility that differences between baseline and follow up are merely a training effect. Long-term effects will thus be assessed at pre-baseline (pBL), baseline (BL), and follow-up 2 months after baseline (FU) (Fig. 2).

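### Effects on sensorimotor function and brain activity are to be judged within as well as between groups, and the pre-baseline visit is credited with excluding training effects; only the comparison with the sham arm can do either job.

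*Protocol article*

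**What the plan says.** The Data analysis section opens with a between-group approach: "Data will be analyzed with repeated measurement methods to compare the intervention group and the control group", and a little further on "Data will be analyzed by inter-group analyses using the Statistical Package for Social Science (SPSS"). It adds "Statistical regression models that adjust for background characteristics and account for correlated measurements for the same individual will also be used", with mixed models and generalized estimating equations as examples. In its last paragraph, on fMRI, it widens the basis for two outcome areas: "The effects of TM on sensorimotor functions and brain activity over time will be studied and compared within and between the intervention and control groups".

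Under Assessments, the article gives the reason for measuring twice before treatment: "One occasion is a pre-baseline assessment in order to exclude the possibility that differences between baseline and follow up are merely a training effect".

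On timing, the inclusion criteria state: "Fifty participants will be recruited from two stroke units in northern Sweden within one week after the onset of stroke". The Intervention section starts treatment one week after onset, on top of ordinary stroke-unit care, and runs it for two weeks. The sensorimotor tests are done at pre-baseline, baseline, week 2 and follow-up two months after baseline (the undefined label WBL, used for two of the tests, is read here as pre-baseline). fMRI is done at baseline and week 2 only.

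**The concern.** Patients are followed from the first week after stroke to about two months after baseline, and all of them receive ordinary care. Both arms can be expected to change whether or not TM works. The Background section says so for brain activity: "longitudinal studies have found that in subjects with good recovery, abnormal activity in motor-related areas is decreased". Hypothesis V predicts much the same pattern, less redundant and more focused activity in motor-related areas, as the result of TM. A before-after difference in the TM arm therefore cannot tell the two explanations apart.

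The pre-baseline rationale has a similar fault. A change between two early assessments is part practice and part recovery, and it covers one repetition in a series of four.

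At stake is a route to a false claim on hypotheses III and V. A significant change under TM beside a non-significant change under sham looks like a treatment effect, but it is not a comparison of the arms. The Discussion presents the trial as groundwork for a multicentre study, so such a claim would carry forward.

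**Working it through.** **The plan's own figure.** The only sample-size figure, 12 per group, is for anxiety (STAI). None is given for the sensorimotor or fMRI outcomes, so there is nothing to reproduce on this point.

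**Inputs from the protocol article.** 25 patients per arm; 15 per arm in the fMRI sub-sample (Power analysis and group distribution).

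**Assumed inputs.** The documents give neither the size of recovery nor the before-after correlation. Taken here: true TM effect zero; the same mean recovery g in both arms, 0.3 or 0.5 between-patient SD; correlation r = 0.7; two-sided 5% tests.

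**Step 1: within-arm test.** The SD of change is √(2(1 − r)) = √0.6 = 0.775 in between-patient SDs. The standardised change is d = g/0.775, that is 0.387 for g = 0.3 and 0.645 for g = 0.5. The paired t-test has noncentrality d√n.

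| g | n per arm | d√n | P(significant improvement in the TM arm) |
|---|---|---|---|
| 0.3 | 15 | 1.50 | 29% |
| 0.3 | 25 | 1.94 | 46% |
| 0.5 | 15 | 2.50 | 64% |
| 0.5 | 25 | 3.23 | 87% |

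At r = 0.5 the SD of change equals the between-patient SD, and the figures are lower: 19% and 30% for g = 0.3, 44% and 67% for g = 0.5 (n = 15 and 25).

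**Step 2: significant under TM, not under sham.** With independent arms and equal recovery this has probability p(1 − p).

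- g = 0.3: 0.29 × 0.71 = 21% (n = 15); 0.46 × 0.54 = 25% (n = 25).
- g = 0.5: 0.64 × 0.36 = 23% (n = 15); 0.87 × 0.13 = 11% (n = 25).

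The product cannot exceed 0.5 × 0.5 = 25%, whatever the recovery.

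**Step 3: between-group test.** Equal recovery cancels in the difference between arms. Simulated two-sample t-tests on change (20,000 runs per setting; common change of 0, 0.5 and 1.0 SD of change) rejected in 4.7% to 5.1% of trials.

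**Step 4: what the pre-baseline visit can show.** Its date is not stated in the text. Recruitment within one week of onset and treatment from one week after onset place it at about the first week. Change from pre-baseline to baseline is then practice plus early recovery, and one number cannot separate them. It also carries no information on practice gained by week 2 or follow-up. The sham arm, tested at the same visits, removes both from the comparison.

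**Step 5: could the pre-baseline visit add precision?** Take residual variance of the outcome, as a fraction of its variance, with baseline alone as covariate: 1 − r².

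- Equal correlations among the three occasions, both covariates: 1 − 2r²/(1 + r). At r = 0.7 this is 0.42 against 0.51, a 17% reduction; over r = 0.5 to 0.8 it is 11% to 20%.
- Correlation decaying with time, AR(1): the pre-baseline score adds nothing once baseline is in the model (0.51 either way at r = 0.7). The mean of the two scores gives 1 − r²(1 + r)/2 = 0.58, which is 14% worse (0.58/0.51 = 1.14). Pre-baseline in place of baseline gives 1 − r⁴ = 0.76.

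**The case against.** The strongest reply is that the trial already plans the right analysis. Two statements in the Data analysis section call for comparison of the groups, the models named account for repeated measurements, and the sentence at issue itself says between as well as within. No rule says that a within-group test decides anything. All of this stands. A reader might infer that the trial's comparative conclusions are confounded with recovery; they are not, because the concurrent sham arm is assessed at the same visits. What remains is that the sentence offers both contrasts as ways to study effects of TM and does not say which one counts. That is a stated choice, not a detail left to an analysis plan.

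A reader might also take 64% and 87% as false-positive rates for a TM effect. They are the chance of detecting a real change, recovery, in one arm. The misleading pattern itself occurs in at most about 25%. All these figures rest on assumed recovery and correlation.

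A third tempting reading is that the pre-baseline score should serve as the covariate throughout. The documents do not support this. fMRI has no pre-baseline visit, the gain depends on the correlation structure, and replacing baseline or averaging with it can lose precision. Nor is the visit without use as planned, since a repeated-measures model could include it.

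Finally, these are secondary outcomes, and the Discussion itself calls the sensorimotor effects more speculative. That limits the weight of the point but does not remove it.

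**Conclusion.** The point holds in a limited form. Within-arm change cannot support a conclusion about TM on hypotheses III and V. With no TM effect and a common recovery of 0.3 to 0.5 SD (assumed, r = 0.7), a within-arm test is significant in about 29% to 64% of trials at n = 15 and 46% to 87% at n = 25. Significance under TM only arises in up to about 25%, against about 5% for the between-group test. The claim that the pre-baseline visit excludes a training effect is too strong; the sham arm does that. The planned between-group inference and the primary outcome stand. The change should be made, because the present wording leaves open a misleading reading and is easily corrected.

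**What to change.** 1. **Data analysis.** State that conclusions on hypotheses III and V rest on the between-group contrast only (group-by-time, or baseline-adjusted difference), and that within-group changes are reported descriptively, with estimates and no tests.

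2. **Assessments.** Replace the training-effect rationale. For example: the pre-baseline assessment serves familiarisation and gives a more stable baseline; training and recovery effects are removed by comparison with the control arm.

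3. **Optional, sensorimotor tests only.** Add the pre-baseline score as a covariate alongside baseline, not in place of it and not averaged with it. The reduction in residual variance to expect runs from none (AR(1)) to about 11% to 20% (equal correlations, r = 0.5 to 0.8).

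Cost: wording only. No visit, patient or measurement is added; the assessments needed are already scheduled.

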### Ethical considerations

The study has been approved by the Regional Ethical Review board in Umeå (2012-110-31). Written informed consent to participate and to publish results will be obtained. The data will be coded and only the research group will have access to the data set and the code list. Double-blind randomization is difficult when assessing effects of massage, and it is common to compare the effects of massage with those during resting. In our study, we have chosen TENS without electric impulses as a sham treatment in order to rule out the possibility that the effects result from receiving any type of treatment whatsoever. The value of this approach is considered to outweigh any possible harm that might result from being subjected to sham treatment and feeling deceived. No physical harm is expected.

## Discussion

TM has been found to have beneficial impacts on a variety of conditions. It increases relaxation and wellbeing in healthy individuals, in the elderly, and in others with a variety of health conditions. It is also noteworthy that we, in an earlier project, found decreased anxiety and pain and increased wellbeing among patients, and further, increased brain activity in areas related to feelings of pleasure and emotional regulation among healthy volunteers. These findings provide reason to believe that TM reduces anxiety and pain, and improves quality of life after stroke. Furthermore, several studies indicate that somatosensory stimulation can increase sensorimotor function, and it is logical to believe that TM increases independence after stroke. Although clinical studies are crucial, they raise several challenges. In Sweden in the 1990′s, high expectations were raised about improved recovery following treatment with acupuncture after stroke. A small study showed promising results of acupuncture in relation to improved motor function and ADL when compared to ordinary care [25]. When repeated in a multicentre trial with two control groups with high intensity and low intensity TENS respectively, acupuncture was not proved to have beneficial effects [57]. In an overview of systematic reviews and meta-analyses [58, 59] effects of acupuncture on disability after stroke were not evident. However, there is some evidence for improved dysphagia and global neurological deficit score. The authors [58, 59] concluded that rigorous RCTs are needed to confirm the results. This illustrates the difficulties in conducting reliable clinical studies and it seems essential to include control groups that receive either a comparable or a non-active treatment to e.g. reduce the Hawthorn effect [60]. In our study we plan to have a control group that receives a non-active TENS treatment as argued for above. Also, sample size is crucial in order to produce reliable results. In our study the sample size is based on results from earlier research that found decreased anxiety after massage treatment in other health disorders. Anxiety is common after stroke and by reducing anxiety it is reasonable to expect that the patient is in a better position to manage the demanding rehabilitation phase. Effects of massage on sensorimotor function is more speculative but theoretically, based on earlier knowledge, it seems reasonable that massage could have positive effects on sensorimotor function. Our study can hopefully guide further well-grounded research within this area. In brief, the present study aims to provide a greater understanding of the effects of TM in rehabilitation after stroke and increase knowledge that will contribute to explanatory models for TM. It is a first step, which we hope will serve as an essential foundation for a future multicentre trial. The results of this project could potentially generate important knowledge for evidence-based care because of the current limited understanding of the effects of TM following stroke.

## Abbreviations

A-State: The state-trait anxiety scale, subscale state
A-Trait: The state-trait anxiety scale, subscale trait
BL: Baseline
BT: Blood pressure
DBE: Department of biomedical engineering
ECG: Electrocardiogram
fMRI: Functional magnetic resonance imaging
FU: Follow up 2 months after baseline
HRQoL: Health related quality of life
HRV: Heart rate variability
Hz: Hertz
MR: Magnetic resonance
mRS: Modified ranking scale
N: Newton
NHP: Nottingham health profile
OCSP: The oxford community stroke project classification
PBL: Pre baseline
PHF: Power of high-frequency
PLF: Power of low-frequency
PTOT: Total spectral power
SPSS: Statistical package for social science
STAI: State-trait anxiety inventory
TENS: Transcutaneous electrical nerve stimulation
TM: Touch massage
TOAST: Trial of org 10172 in acute stroke treatment
UFBI: Umeå center for functional brain imaging
VAS: Visual analogue scale
VLL: Västerbotten county council
W1: After one week intervention
W2: After two weeks intervention
